# *Si-ni-tang* (a Chinese herbal formula) for improving immunofunction in sepsis: study protocol for a pilot randomized controlled trial

**DOI:** 10.1186/s13063-019-3646-3

**Published:** 2019-08-28

**Keywords:** Sepsis, immune function, Protocol, *Si-ni-tang* (SNT), Chinese herbal medicine

## Abstract

**Background:**

Immunologic derangement may be the critical pathophysiologic mechanism in sepsis, and immunotherapy might be a potential new treatment. *Si-ni-tang* (SNT), an ancient Chinese herbal formula documented in *Shanghan Lun*, has been used for treating severe sepsis for thousands of years. Research shows that it may have a therapeutic benefit for sepsis. This study will evaluate the feasibility of testing the effects of SNT on immune function in sepsis patients.

**Methods/design:**

This is a pilot randomized controlled study. Eligible sepsis patients admitted to our medical intensive care unit will be randomly allocated to the control group or the SNT group. Both groups will receive standard therapy according to the recommendations of the Surviving Sepsis Campaign. In addition, the SNT group will receive SNT (150 mL per day for 3 days) orally or by gastric tube, while the control group will receive 150 mL of normal saline. The primary outcome is to assess the feasibility of this treatment. The secondary outcomes include: (1) immune function measured by monocyte human leukocyte antigen-DR (mHLA-DR) expression, procalcitonin, and the ratio of CD4+ to CD8+ T lymphocytes and (2) other clinical data, such as the 28-day all-cause mortality, Sequential Organ Failure Assessment (SOFA) scores, Acute Physiology and Chronic Health Evaluation (APACHE) II scores, both of the latter on days 0 and 3.

**Discussion:**

This study aims to evaluate the feasibility of testing the efficacy of SNT for treating sepsis when used as an adjunctive treatment with the standard therapy recommended by the Surviving Sepsis Campaign.

**Trial registration:**

ClinicalTrials.gov, NCT02777606. Registered on 22 June 2016. Retrospectively registered. https://clinicaltrials.gov/

**Electronic supplementary material:**

The online version of this article (10.1186/s13063-019-3646-3) contains supplementary material, which is available to authorized users.

## Background

Sepsis is a systemic clinical syndrome caused by infectious disease. It is still a major global health problem due to its high incidence and mortality rates, even though supportive care has improved significantly.

During an infection, the immune system is activated to eliminate the pathogen. In sepsis, very often the immune system is over-activated and excessive tissue damage occurs, which results in multi-organ dysfunction [1]. However, studies focused on blocking the hyper-inflammatory response have shown no therapeutic benefit. Indeed, in some cases, this treatment has impacted outcomes negatively [2, 3]. One of the reasons for this failure may be that immune suppression occurs soon after sepsis initiates [4], although immunosuppression is much more frequently observed in the late phase of sepsis. Studies have indicated that both innate and adaptive immunity are suppressed in sepsis, leading to a profoundly decreased production of either pro- or anti-inflammatory cytokines [5, 6], a severe loss of immune cells [7], the downregulation of HLA-DR [6], and impairment of the function of all types of surviving immune cell [5]. Moreover, blocking the hyper-inflammatory response results in an inability to eliminate the pathogen. Therefore, achieving a balance between the hyper- and hypo-inflammatory phases of the immune response against invading pathogens may be a promising treatment for sepsis [8].

*Si-ni-tang* (SNT) consists of *Aconitum carmichaelii Debeaux*, *Zingiber officinale Roscoe*, and *Glycyrrhiza uralensis Fisch*. It was first described in the *Shanghan Lun*, the oldest monograph on infectious diseases, dating back almost 2000 years. SNT is a classical herbal formula prescribed to recuperating patients after a collapse [9], which is a common syndrome observed in sepsis [10]. Furthermore, SNT has been reported to alleviate inflammatory response [11, 12], ameliorate microcirculatory disturbances [13], and improve shock reversal [14] in sepsis in people and animals. However, the effects of SNT on immune function in sepsis have not been comprehensively investigated.

Therefore, the present pilot, a randomized controlled study, has been designed to evaluate the feasibility of using SNT to improve the immune function of sepsis patients.

## Methods/design

### Aim

The study is a prospective randomized controlled pilot trial designed to evaluate, for sepsis patients, the feasibility of testing the effects on immune function of SNT administration in addition to the standard therapy recommended by the Surviving Sepsis Campaign.

### Design

This interventional study will be carried out in the intensive care unit (ICU) of Guangdong Provincial Hospital of Chinese Medicine. It is embedded within an observational study of the immune function of patients with severe sepsis. The trial has received ethical approval from the institutional review board of Guangdong Provincial Hospital of Chinese Medicine (approval number B2016–010.2-01). The investigation will conform to national laws and the Declaration of Helsinki. Eligible participants or their authorized representatives will provide written informed consent before randomization. The protocol adheres to the Recommendations for Interventional Trials (SPIRIT) guidelines (Additional file 1). Figure 1 is a flow chart of the study. If any significant changes must be made to the protocol, a draft of the new version will be submitted for approval from the institutional review board of Guangdong Provincial Hospital of Chinese Medicine.

**Fig. 1 Fig1:**
[figure not shown]
Study flow chart. mHLA-DR monocyte human leukocyte antigen-DR, SOFA Sequential Organ Failure Assessment, APACHE Acute Physiology and Chronic Health Evaluation, PCT procalcitonin, SSC Surviving Sepsis Campaign

Participants can withdraw from the trial for any reason at any time. Researchers can remove participants from the trial to ensure their safety or to maintain the quality of the trial. Participants meeting any of the following conditions may need to be removed from the study: (1) those with severe complications or a deterioration of general health, (2) those violating the study protocol, or (3) those who are lost to the follow-up.

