### Blinding and masking

The laboratory technicians and the biostatisticians responsible for the statistical analysis will be blinded to the assigned treatments. They will not be unblinded under any circumstance.

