Researchers are trained to collect trial data carefully according to a standard protocol. Molecular biomarkers will be measured in triplicate to ensure quality. All data will be input into an electronic database (REDCap 5.7.0, hosted at Peking Union Medical College Hospital) designed for the study. The data will be entered independently into the database by two researchers and will be checked separately by different trained researchers. All collected data forms will be kept in the hospital’s Scientific Research Department.

All adverse events after enrollment to the 28th day after enrollment, regardless of whether they are related to the intervention, will be recorded. All severe adverse events and unexpected adverse events will be reported to the ethics committee within 1 day. The intervention will be suspended if necessary. Symptomatic treatment will be offered when needed. The principal investigator will decide whether patients affected by adverse events should discontinue their participation.

Data and safety will be monitored by the institutional review board of Guangdong Provincial Hospital of Chinese Medicine and the Scientific Research Department of Guangdong Provincial Hospital of Chinese Medicine, which are independent of the sponsor and have no competing interests.

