SNT, a classical herbal formula, has been used for the collapse stage of severe diseases including sepsis in China for thousands of years. It restores *yang* and its warming effect dispels cold [9]. It may have therapeutic effects in patients and animals with sepsis, such as alleviating an inflammatory response [11, 12], ameliorating microcirculatory disturbances [13], and improving shock reversal [14]. However, the effects of SNT on immune function in sepsis have never been investigated. To our knowledge, the present pilot study is the first clinical trial to explore the potential underlying molecular mechanisms and changes in immune function in sepsis due to SNT. The results of this pilot trial may provide insights into the feasibility of a large-scale trial on SNT applied as an adjunctive immunostimulating therapy for a specific subgroup of sepsis patients.

There are several limitations to this pilot study. First, the trial does not have an oral placebo control. When the experimental drug is in the form of granules and powders, an oral placebo can be produced with the same appearance and odor. However, a placebo decoction prepared with distilled water and food coloring to resemble SNT would not have the same smell and taste as the experimental decoctions used in this study. Also, *zhigancao*, a commonly used herb, could not be boiled and used as a placebo decoction alone, since it has a specific pharmacological effect in restoring *qi*. Hence, there is no oral placebo.

Second, this is a pilot trial with a small sample size. The participants are not blinded, and the treatment sepsis patients received is complicated. Hence, this study may not be able to find a significant therapeutic effect.

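### Researchers not listed as blinded may remove deteriorating patients from the study itself, which may undercut the intention-to-treat analysis and leaves unclear who counts as a dropout

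*Protocol article*

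**What the plan says.** All references are to the protocol article.

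- **Design, withdrawal and removal text under Fig. 1.** "Researchers can remove participants from the trial to ensure their safety or to maintain the quality of the trial". Three conditions follow. Patients "may need to be removed from the study: (1) those with severe complications or a deterioration of general health"; the second condition is "those violating the study protocol" and the third is "those who are lost to the follow-up".
- **Data acquisition and assessment of biological data.** "The principal investigator will decide whether patients affected by adverse events should discontinue their participation". This section also records adverse events through day 28, provides bedside or telephone follow-up, and schedules immune data, inflammation data, SOFA and APACHE II at enrolment and 3 days later. It defines dropout as the share of patients lost between enrolment and day 28, and ends that sentence with a clause about outcome data no longer being collected.
- **Blinding and masking.** "The laboratory technicians and the biostatisticians responsible for the statistical analysis will be blinded to the assigned treatments". No other role is listed.
- **Discussion, limitations.** "the trial does not have an oral placebo control", and "The participants are not blinded".
- **Sample size determination.** At least 20 per group, 20% dropout, 50 in total. Because of withdrawals and removals, 52 to 60 random numbers may be used.
- **Outcomes.** Dropout of at most 20% is part of the definition of successful recruitment. The pilot is also meant to supply data for effect sizes in later trials.
- **Statistical analysis.** Intention to treat is named for patients who do not complete the study or its follow-up.

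**The concern.** Getting worse is the clinical course that day-3 SOFA, day-3 APACHE II and 28-day mortality are there to measure. A rule that lets patients leave the study because they got worse makes missing data depend on the outcome. If whoever applies the rule knows the arm, missing data may depend on the arm as well. Protocol violation has a similar problem: the article prohibits immunosuppressive and immunoenhancing therapy, so a patient given such therapy for clinical reasons could be removed.

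Two things are at stake. The first is the between-arm comparison of secondary outcomes that is meant to inform a larger trial. The second is the 20% dropout criterion, which belongs to the primary feasibility endpoint and depends on who counts as lost.

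**Working it through.** **1. Removal grounds against outcomes.** Study treatment lasts 3 days and the marker and severity outcomes are read on day 3. Removal for deterioration, complications or an adverse event before then can cost the day-3 values. Removal at any time up to day 28 can cost the mortality status. All these events happen after randomisation.

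**2. Who decides.** The deciders are researchers and, after adverse events, the principal investigator. The blinded list names only laboratory technicians and biostatisticians. The control is saline against a herbal decoction, with no matching placebo. The article does not say that the deciders know the arm, but nothing in it prevents this.

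**3. Whether intention to treat repairs it.** Intention to treat settles the arm in which a patient is analysed. It cannot supply a day-3 sample or a day-28 status that was not collected. The follow-up and adverse-event text neither includes nor excludes removed patients.

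**4. Possible size for mortality.** Inputs: 50 planned and 1:1 allocation, so 50/2 = 25 per arm. The number removed, k, is an assumption. If k patients in one arm have unknown day-28 status, that arm's mortality is undetermined over k/25:

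- k = 1: 1/25 = 4 points
- k = 3: 3/25 = 12 points
- k = 5: 5/25 = 20 points

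This holds whatever the mortality. As an illustration, assume 40% mortality (10/25) and that the removed patients would all have died and are left out of one arm:

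- k = 1: 9/24 = 37.5%, a shift of 2.5 points
- k = 3: 7/22 = 31.8%, a shift of 8.2 points
- k = 5: 5/20 = 25.0%, a shift of 15.0 points

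If the same patients are followed, the result stays at 10/25 and the shift is zero.

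**5. The dropout criterion.** The plan's total reproduces: 2 × 20 = 40, and 40/(1 − 0.20) = 50. The limit is 0.20 × 50 = 10 patients. Assume 50 randomised, 5 lost to contact and 6 removed, of whom f still have their outcomes collected:

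- Only loss of contact counts: 5/50 = 10%, met.
- Every removal counts: (5 + 6)/50 = 22%, not met.
- Only patients without further data count: (5 + 6 − f)/50, which is 10% at f = 6, 16% at f = 3 and 22% at f = 0.

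Not every data set is affected. With 5 lost and 4 removed, the first two readings give 10% and 9/50 = 18%, and both meet the limit.

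**The case against.** The strongest reply is that nothing states that follow-up ends at removal, and some text leans the other way. Adverse events are recorded to day 28 with no exception, telephone follow-up exists, and intention to treat is named for the very patients who do not complete. An article may also leave the handling of data after discontinuation to the full protocol. This stands to the extent that loss of data is permitted by the printed rule but not shown to occur. It does not remove the point, because the rule itself is printed and removes patients from the study.

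Removal is also discretionary, the clinical and immune outcomes are secondary, and the article already discloses the small sample, the missing placebo and the unblinded participants. All of this limits the importance of the point.

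Three stronger readings are tempting and are not supported:

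- **That removed patients are replaced and leave the analysis.** The reserve of random numbers suggests replacement, but randomising more than 50 is compatible with analysing everyone. Intention to treat is at risk of being undercut; it is not contradicted.
- **That the 2 to 10 extra random numbers are the count of removals.** With 10 lost, this would give dropout of 12/52 = 23.1% to 20/60 = 33.3%. It would also leave the mortality difference undetermined over 2/26 = 7.7 to 10/30 = 33.3 points. The article ties the extras to withdrawals as well as removals, and 52 is the first multiple of the block size of four above 50, so the lower figure may partly reflect completing a block.
- **That the dropout criterion necessarily yields opposite verdicts, or may be divided by 50 when more are enrolled.** The closing clause of the definition can be read to count only patients without further data, which gives one verdict. Counting losses from enrolment points to all enrolled patients as the denominator.

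**Conclusion.** The point holds as a weakness in a printed rule. Researchers who are not listed as blinded may take patients out of the study on grounds tied to the outcomes, and the article does not say that such patients are still followed. This may undercut the intention-to-treat analysis and bias the secondary comparisons that are to feed a future trial.

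The size cannot be stated because no removal rate is given. The figures of 4 to 20 points per arm rest on 1 to 5 assumed removals with unknown status. They are limits, not expected bias, and they become zero if removed patients are followed.

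The dropout point is secondary. The definition is unclear on removed patients and may be read in more than one way, and whether this changes the verdict depends on counts that are not yet known. The planned total of 50 is correct. For a feasibility pilot this is worth an amendment but does not threaten the trial as a whole.

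**What to change.** **Design, and the adverse-event text under Data acquisition.** Suggested wording: *Severe complications, deterioration, adverse events or protocol violation may lead to stopping study treatment, by decision of the investigator, but not to ending participation. Unless consent is withdrawn, these patients are sampled on day 3 if alive, followed to day 28 and analysed in the arm to which they were randomised. Any prohibited therapy is recorded and summarised by arm.*

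**Dropout definition under Data acquisition.** Suggested wording: *Dropout is withdrawal of consent or unknown day-28 status, over all randomised patients. Stops of study treatment are reported separately by arm and are not dropouts.* A death then has a known status and is not a dropout. In the example above, with the 6 removed patients followed, the rate is 5/50 = 10% and there is only one reading.

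**Cost.** The edits are short and use only assessments already on the schedule. If removal currently ends data collection, some of those samples and contacts will be work that would otherwise not have been done. Recruitment is under way, so this is an amendment that needs review-board approval. For patients already removed, day-28 status should be sought where consent allows. The downside is that some day-3 marker values will carry the effect of stopped treatment or prohibited therapy, which adds noise to the marker comparison.

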#### Inclusion criteria

The inclusion criteria for the observational study [15] are as follows:
Aged between 18 and 85Documented or suspected infectionTwo of the following induced by the infection:
rectal temperature between 38 °C and 36 °Cheart rate >90 beats per minuterespiration rate >20 breaths per minute, partial pressure of carbon dioxide in arteries pa CO_2_ < 32 mmHg, or requiring ventilationwhite blood cell count >12 × 10^9^ L^-1^ or <4 × 10^9^ L^-1^, or immature forms of white blood cells >10%One of the following:
arterial hypotension (systolic blood pressure, SBP < 90 mmHg, mean arterial pressure <65 mmHg, or SBP decrease >40 mmHg in adults or vasopressor-dependent to maintain SBP ≥ 90 mmHg or mean arterial pressure ≥ 65 mmHg) persisting for 1 hour or more in spite of adequate fluid resuscitationoxygenation index ≤300pH ≤ 7.30 or base excess ≤ –5.0 mmol L^-1^ with hyperlactatemia (≥3 mmol L^-1^)acute oliguria (urine output <0.5 mg kg^-1^ h^-1^ for at least 2 hours), creatinine increase >2 mg dL^-1^ within 48 h, or requiring renal replacement therapyhyperbilirubinemia (plasma total bilirubin > 2 mg/dL or 35 μmol L^-1^)platelet count < 10 × 10^12^ L^-1^international normalized ratio >1.5 or activated partial thromboplastin time >60 s

The inclusion criteria for the interventional study are as follows:
Meet all the criteria for the observational part*Yin* syndrome, presenting some of the following [16]:
sudden drop of body temperature or cold extremitiesfatiguepale complexiondull paincold sweat or sticky sweatdull purplish or pale tonguefaint or deep slow pulse

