### Sample size determination

There are no previous clinical studies on using SNT to improve immune function in sepsis, and because of the pilot nature of this study, we need to recruit at least 20 participants in each group to achieve sufficient precision for a sample size calculation in a subsequent full trial [17]. With a 20% dropout rate, we plan to recruit a total of 50 participants. Moreover, since participants can withdraw or may be removed from the trial, 52–60 random numbers may ultimately be needed. Thus, the final number of participants in each group may be differ.

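### Platelet, temperature and urine-output entries in the inclusion criteria are wrong as written; taken literally, the platelet limit makes the organ-dysfunction requirement exclude nobody with a platelet count

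*Protocol article*

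**What the plan says.** The Inclusion criteria section of the protocol article sets out the observational study's criteria: an age range, infection, two of four inflammatory-response items, and an organ-dysfunction group introduced by "One of the following". That last group has seven items.

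- **Platelets.** One of the seven is "platelet count < 10 × 10^12^ L^-1".
- **Urine output.** The oliguria item, also one of the seven, includes "urine output <0.5 mg kg^-1^ h^-1^ for at least 2 hours".
- **Temperature.** The first inflammatory-response item is a rectal temperature lying between the two limits 38 °C and 36 °C. The heading over that group says the items must be caused by the infection.
- **White cells.** The item in the same group counts values above 12 or below 4, in units of 10^9/L.

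The randomized study takes these criteria over in full: "Meet all the criteria for the observational part". It then adds yin syndrome and a list of exclusions. No other section restates or corrects the three entries.

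**The concern.** A limit that every patient meets cannot select. Because the organ-dysfunction group is an any-one-of-seven rule, one item that is always true satisfies the whole group. The temperature item appears inverted: it gives credit for values inside a band, under a heading that asks for signs caused by infection and beside a white-cell item that counts values outside a range. The urine item uses milligrams for a volume. Three faults in one short list suggest careless transcription.

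Eligibility matters here beyond the description of the sample. The primary endpoint is feasibility. Under Outcomes, success requires enrolling at least 50% of eligible patients, and the section on data acquisition defines the recruitment rate with eligible patients as its denominator. The pilot is also meant to supply effect-size inputs for a later trial, with 28-day mortality and SOFA among its secondary endpoints. If the written limits are applied, these figures describe a population other than the severe sepsis patients named under Design. If other limits are applied, the text no longer says who is eligible, and the Design section allows removal of participants who violate the protocol.

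**Working it through.** No figure in the plan can be reproduced for the platelet limit. The check is unit conversion and logic.

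**Platelet limit**

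Input: 10 × 10^12 per L (Inclusion criteria).

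Conversion to the unit used for white cells in the same list: 10 × 10^12 ÷ 10^9 = 10,000, so the limit is 10,000 × 10^9/L.

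The documents give no human platelet range, so one is assumed: usual counts of 150–450 × 10^9/L, tested over a much wider span.

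| Assumed count (× 10^9/L) | Limit ÷ count | Below the limit? |
|---|---|---|
| 20 | 500 | yes |
| 150 | 66.7 | yes |
| 450 | 22.2 | yes |
| 2,000 | 5 | yes |
| 5,000 | 2 | yes |

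The item is met at every count tested.

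**Organ-dysfunction rule (any one of seven)**

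With the platelet item true, the other six items can take 2^6 = 64 combinations. The rule is met in all 64, including the one where none of the six is present. The requirement therefore excludes nobody who has a platelet count.

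**Temperature item (two of four needed)**

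Read as written, 36.5, 37.0 and 37.5 °C earn credit; 35.0, 35.9, 38.1, 39.0 and 40.0 °C do not. Let k be the number of the other three items met (heart rate, respiration, white cells). As written, a patient inside the band scores k + 1 and a patient outside it scores k.

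| k | Inside 36–38 °C | Outside 36–38 °C |
|---|---|---|
| 0 | 1, not met | 0, not met |
| 1 | 2, met | 1, not met |
| 2 | 3, met | 2, met |
| 3 | 4, met | 3, met |

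The item decides the outcome only at k = 1. There it admits the patient inside the band and rejects the one outside; an outside-the-band reading would reverse both results. At k = 0, 2 or 3 the direction of the item makes no difference.

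**Urine output**

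A rate in mg per kg per hour is a mass rate, while urine output is measured as a volume. No further calculation applies.

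**What is not affected**

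The sample size stands apart from these entries. The plan says "we need to recruit at least 20 participants in each group" and "With a 20% dropout rate, we plan to recruit a total of 50 participants": 2 × 20 = 40, and 40 ÷ (1 − 0.20) = 50, which matches the stated total.

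**The case against.** The best defence is that the harm depends on literal application, which the article does not show. Under Interventions and procedures, investigators are to be trained and given a printed protocol and a case report form. Neither is shown, and both may carry the intended limits. The entries look like transcription slips. This stands: the effect on actual enrolment is unknown, and every downstream consequence must be stated conditionally. It does not remove the point, because eligibility limits are stated here and stated wrongly. A text-reading fault is an unlikely explanation, since the exponent 12 is explicit beside the exponent 9 used for white cells, and a lost symbol would not turn an outside-the-range item into one worded as lying between two limits.

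The second defence is that temperature seldom decides anything. Candidates are ICU patients, and the respiratory item can be met by needing ventilation, so two other items may often be present. The condition k = 1 stands as a real limit on the effect, but the documents give no figure for how often it occurs.

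The third is that other requirements remain: age, infection, the two-of-four rule, yin syndrome judged by two senior physicians, and the exclusions. This also stands. Only the organ-dysfunction requirement loses its force.

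A reader might also see a contradiction between the temperature item and the yin sign of a sudden fall in temperature. The text does not support that. A fall is a change and not a level, so a drop from 39 to 37 °C fits both. Cold extremities alone meet that sign, and only some of the yin signs are required.

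**Conclusion.** The point holds as a fault in the written criteria. The platelet limit is 10,000 × 10^9/L, so the organ-dysfunction requirement as printed excludes no patient with a platelet count. This rests on an assumed human range, but the conclusion is unchanged from 20 to 5,000 × 10^9/L. The temperature item credits the wrong side of its band, judged against its own heading and the neighbouring white-cell item, with consequences only when exactly one of the other three items is met. The urine unit is a minor fault.

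Two stronger readings might be inferred and are not supported. One is that the trial is restricted to patients at 36–38 °C; the two-of-four rule imposes no such restriction. The other is that the recruitment rate, event rates and SOFA estimates are already distorted; that would require literal application, which the documents do not establish. What can be said is that either the text is followed and patients without organ dysfunction can enter, or it is not followed and practice departs from the written criteria. Both are reasons to correct it while recruitment is still open, as the Trial status section says it is.

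**What to change.** 1. Reconcile the temperature, platelet and urine-output entries in the Inclusion criteria with the source cited for them (reference 15), and check that the case report form agrees. That source is not at hand, so no replacement limit is proposed here.
2. Go through the screening log once for patients who qualified only through the temperature or the platelet item.
3. Only if any are found, flag them and report the recruitment rate and the secondary outcomes with and without them. If none are found, a text correction is enough.

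The cost is a correction to the protocol text and case report form, plus one pass through the screening log. The planned total of 50 does not change.
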